## Abstract

**Introduction:**

Despite the benefits of early diagnosis, most cancers in sub-Saharan African (SSA) countries are diagnosed at an advanced stage due to late presentation of symptoms, inadequate referral systems and poor diagnostic capacity. Health communication interventions have been used extensively in high-income countries to increase people’s awareness of cancer symptoms and encourage timely help-seeking. However, in SSA, there is still limited evidence on the effectiveness of these interventions and existing evaluations are mainly focused on communicable diseases rather than cancer.

**Methods and analysis:**

A randomised, multisite, controlled community trial will evaluate a culturally tailored health infographic toolkit delivered in rural and urban settings in the Western Cape Province in South Africa and Harare and surrounding provinces in Zimbabwe. Participants will be randomised to receive one of three African aWAreness of CANcer and Early Diagnosis (AWACAN-ED) cancer awareness tools, coproduced with local communities, comprising health communication infographics with descriptions of breast, cervical and colorectal cancer symptoms plus messages to encourage consultation with primary care providers if symptoms occur, all presented in English and four local languages. We will recruit 144 participants in each of the three intervention groups (N=432). The primary outcome will be recall of symptoms and the secondary outcomes will be (1) intention to seek help, (2) emotional impact and (3) acceptability of the toolkit. Outcomes will be measured preintervention and at two points postintervention: after 15 min and 1 month.

**Ethics and dissemination:**

Ethical approval was obtained in both participating countries, South Africa (148/2025) and Zimbabwe (363/2021). All participants will be required to provide written informed consent prior to participation. Findings will be disseminated through peer-reviewed publications, conference presentations and the AWACAN-ED programme website.

**Trial registration number:**

PACTR202505475803308.

STRENGTHS AND LIMITATIONS OF THIS STUDYThe study will test the psychological impact of culturally sensitive health messaging and infographics in English and four local languages in the African aWAreness of CANcer and Early Diagnosis (AWACAN-ED) public toolkit to investigate emotional response to engagement with the toolkit.Engagement of community members of different ages in the codesign and development of the intervention to enhance cultural appropriateness.Although each South African and Zimbabwean province was selected to be representative of rural and urban communities, they may have limited generalisability across the two countries and across sub-Saharan Africa.The trial will only measure the short-term impact of the AWACAN-ED public toolkit.

## Introduction

 Stage at diagnosis is a major determinant of cancer outcomes. In sub-Saharan African (SSA) countries, studies estimate that patients diagnosed with breast, cervical or colorectal cancer at an early stage (I/II) had 50%–62.5% 5-year survival probability compared with a 5-year survival of 20.5%–35.8% for those diagnosed at an advanced stage (III/IV).^1^,^3^ Despite early diagnosis leading to treatment with curative intent, most cancers in SSA are diagnosed at advanced stages. Studies estimate that in SSA, 64%, 66% and 70% of breast,^1^ cervical^2^ and colorectal^4^ cancers are diagnosed at an advanced stage, respectively. The main determinants of this advanced cancer diagnosis in SSA are late presentation of symptoms, inadequate referral systems and poor diagnostic capacity.^5^

The WHO recommends early diagnosis strategies for breast, cervical and colorectal cancers as a priority control measure in low-income and middle-income countries (LMICs), where cancer screening programmes are either not effectively implemented or non-existent.^6^ One strategy is to increase people’s awareness of symptoms and encourage timely presentation to healthcare professionals when symptoms occur.^7 8^

Health communication strategies aim to raise awareness of risk factors and symptoms, reinforce positive actions, influence social norms and change individual or group attitudes and behaviours.^9^ They can use different delivery formats, from conventional printed materials (eg, posters, leaflets, brochures) and broadcasting (eg, radio, television (TV), film) to digital messaging and social media (eg, X, Facebook, TikTok, WhatsApp). They can also use different design approaches from educational programmes and community outreach to printed or digital infographics. Successful health communication interventions will depend on how well contextual elements, such as linguistic and cultural differences, as well as health belief systems and values of the target population are incorporated in the design and implementation of the communication strategies.^10 11^ Thus, the development of health communication interventions must include extensive formative research, needs assessments and message pretesting.^9^

Although most evidence on health communication interventions aiming at increasing cancer awareness and encouraging help-seeking has been generated in high-income countries,^12 13^ there are examples of culturally tailored interventions conducted in LMICs with positive outcomes. For example, a successful health communication intervention to raise breast cancer awareness in India adopted a multilingual approach and segmented the target population into key homogenous groups based on religion and education levels.^14^ Whereas women with higher education levels were presented with a combination of facts and statistics related to breast cancer, women with lower education levels were given an educational programme using posters, presentations and leaflets adapted to their language and beliefs.^14^ Similarly, in Malaysia, another effective public awareness intervention for breast and colorectal cancer symptoms was culturally adapted for the three main ethnicities of the country. The intervention, a mass media campaign based on the UK’s ‘Be Cancer Aware’ programme and involving TV and radio advertisements and print materials (eg, billboards, posters), was adapted to the populations’ main languages (Malay, Chinese, Indian) and considered religious and other cultural values.^15^ In Africa, a systematic review, including evaluation studies in Nigeria, Tanzania, South Africa, Kenya, Malawi and Zambia, and another study conducted in Cameroon also demonstrated a positive impact of health education (eg, didactic lectures) and health communication (eg, information leaflets, videos) interventions on cervical cancer awareness.^16 17^ However, evidence on the effectiveness of these interventions in Southern Africa is still limited and the existing studies are mainly focused on addressing communicable diseases (COVID-19, HIV, Ebola), rather than cancer.^10^

This evaluation fills an essential gap by assessing the impact of research-informed and culturally tailored health communication interventions to improve awareness about cancer symptoms and to encourage timely help-seeking. The study is part of the NIHR-funded African aWAreness of CANcer and Early Diagnosis (AWACAN-ED) research programme, which aims to develop and evaluate tools for timely symptomatic diagnosis of cancer (https://awacan.online/). The overall aim of this study is to evaluate the efficacy of the AWACAN-ED public toolkit, which consists of a portfolio of locally tailored, context-sensitive and multilingual (English, Afrikaans, isiXhosa, Ndebele and Shona) infographics with health messaging delivered in both a rural and an urban setting in large regions in South Africa (Western Cape Province) and Zimbabwe (Harare and surrounding provinces). The primary objective is to test the impact of the exposure to the AWACAN-ED public toolkit on the recall of symptoms of breast, cervical and colorectal cancer. The secondary objectives are to examine the impact of the AWACAN-ED public toolkit on (1) the intention to seek help for symptoms of possible breast, cervical and colorectal cancer, (2) the emotional impact and (3) the acceptability of the toolkit.

## Methods and analysis

### Study design

The AWACAN-ED public toolkit study is a three-arm parallel-group randomised controlled multisite, community superiority trial. The study protocol reports in adherence with the Standard Protocol Items: Recommendations for Interventional Trials guideline.^18^,^20^ The main hypotheses of this randomised control trial (RCT) are that the exposure to the AWACAN-ED public tool will improve the recall of symptoms of breast, cervical and colorectal cancer and enhance the intention to seek timely help for symptoms of possible cancer, without increasing anxiety.

### Eligibility criteria and recruitment process

Participants will be eligible for the trial if they are at least 18 years old and reside in the selected study areas. Participants will be excluded if they fulfil any of the following exclusion criteria:

Previous self-reported diagnosis of breast, cervical or colorectal cancer.Unable to communicate in English, Afrikaans, isiXhosa, Ndebele or Shona.Unable to provide informed consent.

The sample will be recruited in community-based sites, such as community centres, churches and at local events, with the assistance of members of the community advisory boards in the Western Cape (South Africa) and Harare and surrounding provinces (Zimbabwe). Previous AWACAN-ED health facility assessments informed the selection of these areas, which represent rural and urban communities and are comparable in size and population. Experienced field workers will approach potential participants, check eligibility, invite them to participate in the study and gain written informed consent. Both women and men will be included, but we will recruit more women than men (ratio 2:1). The inclusion of men in the evaluation of the cervical and breast cancer tools responds to the important role that male partners play in women’s help-seeking behaviour for cancer reported in the literature^21^ and was emphasised during our community workshops. Recruitment will last up to 6 months.

### Randomisation, intervention allocation and blinding

After consent is obtained, participants will be asked to complete a preintervention survey in their chosen language (English, Afrikaans, isiXhosa, Ndebele and Shona), including sociodemographics and any previous experience of breast, cervical and colorectal cancer among family and friends. Participants will then be randomly assigned to the exposure to one of the three (allocation ratio 1:1:1) cancer infographic tools (either breast, cervical or colorectal cancer). There will not be a ‘no intervention’ control group: each participant will only be exposed to one cancer tool and will act as the control group for the two other cancer tools.^22^ We have not included a ‘no intervention’ control group due to ethical concerns of withholding information about cancer symptoms to communities who are known to lack access to information and have low cancer awareness, but also due to the likelihood of participant demoralisation and attrition for taking part in a study but receiving no intervention. However, it is acknowledged that this prevents insight into the impact of multiple completions of the same survey. Simple randomisation techniques will be used in each of the four study settings using an online randomisation service (eg, www.sealedenvelope.com) (see study flow chart in figure 1). Due to the overt nature of the intervention, blinding participants and fieldworkers will not be possible, but data analysts will be blind to group and the allocation sequence will be concealed from the person allocating participants to the interventions using sealed opaque envelopes.

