### Outcome measures

The preintervention (T0) assessment will include sociodemographic questions (age, gender, relationship status, education and language most spoken at home), and any previous knowledge and experience of breast, cervical or colorectal cancer among family and friends.

To evaluate the efficacy of the AWACAN-ED public toolkit, we will measure two outcomes before (T0) and at two points after the intervention (T1: 15 min after the intervention; T2: 1 month after the intervention): recall of symptoms (primary outcome) and intention to seek help (secondary outcome). See study instrument in online supplemental material 1.

To assess recall of symptoms, an open-ended question will be used: *“Please would you name as many symptoms or signs of [breast, cervical, or colorectal] cancer as you can think of?”*.^27^ Responses will be recorded verbatim and will be coded by two researchers in each country against an agreed list of symptoms from the AWACAN survey for breast (15 symptoms) and cervical (11 symptoms) cancer awareness^27^ and from the Bowel Cancer Awareness Measure (9 symptoms).^28^ Participants will score ‘1’ if they mention a symptom that corresponds to the list of symptoms, and ‘0’ if they do not mention it and summed to produce total score of the number of recalled symptoms for each cancer type.

Intention to seek help will be measured by asking participants to report how soon they would visit the pharmacy or clinic or health centre or hospital, if they noticed symptoms of possible breast, cervical and colorectal cancer^27^ with five response options (‘never’, ‘less than 1 week’, ‘between a week and 1 month’, ‘between a month and 3 months’ and ‘3 months or more’). Only women will be asked the items about seeking help for breast or cervical symptoms. For analysis, responses will be dichotomised to ‘less than 1 week’ and ‘more than 1 week’.

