### Sample size and data analysis plan

Participant characteristics and outcomes will be summarised using descriptive statistics, including mean and median, SD and IQR. To assess how engaging participants found the health communication tools, we will use descriptive statistics to report the proportion of participants who agreed with each aspect of engagement. For the open response question, two researchers will independently code the responses into thematic categories.

We have estimated the sample size based on the assumption that the baseline number of expected recalled symptoms before the intervention will be equivalent to the average number of breast cancer symptoms recalled in South Africa using the same measure.^32^ The expected effect of the intervention on symptom recall was assumed to match or exceed the increase observed in a comparable study of lung cancer symptom recall in the UK^33^ that had a more conservative impact than a recent quasi-experimental study in South Africa.^34^ Based on these assumptions, a sample size calculation for a paired t-test with a significance level (α) of 0.05 and a power of 80% resulted in an estimated requirement of 144 participants per intervention group (N=432). This will be distributed across the two settings in South Africa and two in Zimbabwe (see table 1). To allow subgroup analyses by gender, age band and language, we will recruit at least 20 participants to each category and recruit twice as many women (n=288) as men (n=144). We anticipate minimal missing data as the questionnaires will be administered by experienced fieldworkers and researchers. However, listwise deletion will be used if any data is missing at random. Statistical analyses will be conducted using R software (2021).^35^

**Table 1 T1:** Planned minimum sample sizes required and distribution by intervention group

Research site	Intervention groups			Total
	Breast cancer tool	Cervical cancer tool	Colorectal cancer tool	
South Africa (Western Cape)				
Urban	36	36	36	108
Rural	36	36	36	108
Zimbabwe (Harare)				
Urban	36	36	36	108
Rural	36	36	36	108
Total	144	144	144	432

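### The design makes participants controls for the two cancers they are not taught, but the sample size rests on a within-arm paired t-test, so the stated 80% power does not carry over to the controlled comparison

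*Protocol article*

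**What the plan says.** All places are in the Protocol article.

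- **Introduction:** the main aim is worded as follows: "test the impact of the exposure to the AWACAN-ED public toolkit on the recall of symptoms of breast, cervical and colorectal cancer".
- **Study design:** the trial is a "three-arm parallel-group randomised controlled multisite, community superiority trial".
- **Randomisation, intervention allocation and blinding:** the arms have an "allocation ratio 1:1:1" and there is no untreated arm; instead, "each participant will only be exposed to one cancer tool and will act as the control group for the two other cancer tools". The same paragraph concedes that, without an untreated arm, the effect of repeated survey completion cannot be seen.
- **Outcome measures:** answers to an open recall question are coded against lists of 15 (breast), 11 (cervical) and 9 (colorectal) symptoms and "summed to produce total score of the number of recalled symptoms for each cancer type". This is done at T0 and twice afterwards ("T1: 15 min after the intervention; T2: 1 month after the intervention").
- **Sample size and data analysis plan:** the size comes from "a sample size calculation for a paired t-test with a significance level" of 0.05 and 80% power, giving 144 per intervention group and 432 in all. The section gives no mean change, SD or correlation. It names no other inferential test and no between-arm or pooled contrast.

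**The concern.** A paired t-test within one arm of 144 is a before-after comparison. It uses neither the 288 concurrent participants who were not taught that cancer nor each person's two untaught scores. The control structure that justifies calling the trial controlled therefore plays no part in the calculation that fixed its size.

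Two things are at stake.

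- **Bias.** T1 follows T0 in the same session and repeats the question, so a within-arm gain mixes the tool's effect with retesting. The untaught scores are what would separate the two. The article's remark that it cannot learn about repeat completion fits a pre-post reading and sits badly with the control role it gives participants just before.
- **Power.** If the analysis uses the randomised contrast, the 80% was computed for a different comparison and need not apply.

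**Working it through.** **Inputs from the article.** 144 per arm, three arms, 432 in total; paired t-test, alpha 0.05, power 80%. Table 1 agrees: 36 x 4 = 144 and 36 x 12 = 432.

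**Assumptions, because the article is silent.** Two-sided test; equal SD across cancers; pre-post correlation rho from 0 to 0.7; correlation r between a person's scores for different cancers (changes, or T0-adjusted residuals) from 0 to 0.5; the same standardised effect for each cancer; no spillover and no loss to follow-up. That everyone answers for all three cancers is inferred from the control role and the per-cancer totals, since the instrument is in a supplement not shown.

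**1. The plan's own figure.** With no effect size or SD given, 144 can only be inverted. Standardised change = (1.960 + 0.842)/sqrt(144) = 0.233 by the normal approximation, or 0.235 with the noncentral t. (One-sided at 0.05 it would be 0.207 or 0.208.)

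**2. One cancer, randomised contrast, change scores.** In units of the SD of change:
- SE = sqrt(1/144 + 1/288) = sqrt(1/96) = 0.102
- Power = Phi(0.2335/0.102 - 1.96) = Phi(0.33), about 63%

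**3. The same contrast with T0 adjustment.** The effect in raw SD units is 0.2335 x sqrt(2(1 - rho)), and the SE is sqrt((1 - rho^2)/96). Their ratio is 0.2335 x sqrt(192/(1 + rho)).

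| rho | ratio | power |
|---|---|---|
| 0.3 | 2.84 | 81% |
| 0.5 | 2.64 | 75% |
| 0.7 | 2.48 | 70% |

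**4. Pooled taught-v-untaught contrast, change scores.** Each person contributes the taught change minus the mean of the two untaught changes, with variance 1 + (1 + r)/2 - 2r = 1.5(1 - r). Averaged over 432 people, SE = sqrt(1.5(1 - r)/432) = sqrt((1 - r)/288). Simulation (8,000 runs at each r) gave matching values: 0.0586, 0.0490 and 0.0427.

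| r | pooled SE | v one-cancer contrast (0.102) | v one arm's paired change (1/sqrt(144) = 0.083) | v mean of three paired changes (1/sqrt(432) = 0.048) |
|---|---|---|---|---|
| 0 | 0.059 | 42% smaller | 29% smaller | 22.5% larger |
| 0.3 | 0.049 | 52% smaller | 41% smaller | 2.5% larger |
| 0.5 | 0.042 | 59% smaller | 50% smaller | 13% smaller |

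The last column breaks even where (1 - r)/288 = 1/432, that is, at r = 1/3. With T0 adjustment it runs from 38.8% smaller (rho 0, r 0.5) to 12.9% larger (rho 0.7, r 0).

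Pooled power at the implied effect is Phi(0.2335/0.0589 - 1.96) = Phi(2.00), about 98% at r = 0, and over 99% at r = 0.3.

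**The case against.** **The paired t-test is named only for sizing.** A reader might infer that it is the primary analysis and that the trial has no toolkit-level estimate. The article says neither. It is a condensed account, and the model may stand in a full protocol or analysis plan not shown. The superiority label and the control role even point towards a controlled analysis. This stands, and it limits the point to what the article does state: a size and power calculated for a comparison that its own design does not rely on.

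**The precision loss is easy to overstate.** A reader might infer that the named test throws away more than 40% of the available precision. The 42% is measured against a 144 v 288 contrast that the article does not name. Against the paired test, the saving on change scores is 29% at r = 0, and the correlations are not in the document. Against the mean of three paired changes there may be no saving. At r = 0 the whole step from 0.102 to 0.059 is the factor 1/sqrt(3) from averaging three estimates, which changes the estimand from one cancer to three. Nor is the within-person contrast a separate source of information: with equal arms it is algebraically the average of the three between-arm contrasts. All of this stands.

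**Pooling is a choice.** Three tool-specific effects are a fair reading of an objective that lists three cancers, and an average could hide a tool that fails. This stands against a pooled effect as the sole primary result, but not against reporting it beside the three. It leaves the bias argument untouched, because the mean of three paired changes is also uncontrolled.

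**Conclusion.** The mismatch is real. The article describes a randomised design with participants as controls for their untaught cancers and states its objective for the toolkit, but it sizes the trial on an uncontrolled within-arm test and states no controlled or toolkit-level contrast. At the effect that 144 implies, the single-cancer randomised contrast has about 63% power on change scores. With T0 adjustment it has 81%, 75% and 70% at rho 0.3, 0.5 and 0.7, so 80% is reached only when the pre-post correlation is low. The pooled contrast has ample power, about 98% or more, if the effect is similar across tools and spillover is small.

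The main reason to change is bias: comparing taught with untaught under randomisation balances retesting, which no set of paired tests can do. It does not remove any effect of unblinded participants or fieldworkers that is specific to the taught cancer. These figures rest on the assumed correlations and on all three recall questions being put to everyone.

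**What to change.** State in the article, or in the analysis plan it refers to, that recall is analysed as taught v untaught:

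- Put each recall score on a common scale (divided by its T0 SD, or as a share of its symptom list).
- Fit one model over all three scores with fixed effects for cancer type, own-tool (yes/no), T0 recall and setting, and a participant random effect.
- Report the three cancer-specific effects from the own-tool x cancer term alongside the pooled toolkit-level effect, and say in advance which is primary.
- Restate the power for that contrast, giving the assumed effect, SD and correlations, and give any precision gain as a range over those correlations.
- Reword the remark on repeat completion: change in the untaught scores does carry information on it, mixed with any spillover.

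The cost is some wording and one model, with no new data, and it should be settled before the analysts are unblinded. There are two downsides. The pooled figure averages three tools on a constructed scale, and spillover from the taught cancer to the others shrinks it towards zero.
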